### Blinding

The participants will be blinded to the allocation to the different groups. One researcher will be in charge of the randomization process and will program the laser device based on the results of the randomization. A second researcher will perform the LLLT and will be blinded to the doses and respective groups. These researchers will not participate in any of the evaluation phases, which will be performed by a third researcher blinded to the allocation of the subjects to the different groups. When blood collection is involved, the evaluations will be performed by an experienced, trained nurse, who will only participate in these evaluations. The statistician will be blinded to the group allocation until completion of the statistical analyses.

### Inclusion criteria

Diagnosis of DM-2 confirmed by the participant’s physician; age between 30 and 70 years; either gender; sufficient cognitive level for understanding the procedures and following the instructions; and agreement to participate in the study by signing of a statement of informed consent after receiving clarifications regarding the objectives.

### Exclusion criteria

Diagnosis of cardiovascular disorder; hepatic diseases; pernicious anemia; diagnosis of diabetic neuropathy; occurrence of skin lesion or local infection over the quadriceps muscle; history of skeletal muscle injury in previous six months or during the execution of the study; inability to perform exercise protocol or undergo evaluations in a satisfactory manner; current practice of regular physical activity; and chronic joint disease in lower limbs. Exclusion criteria will be determined by access to medical history of individuals.

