[21] the execution of physical exercise. This therapeutic modality seems to improve muscle performance via the energy metabolism in cells by stimulating photochemical events and enhancing mitochondrial function in muscle cells
[22]. The structural changes in the mitochondria (size) promoted by LLLT lead to an improvement in cell respiration and the formation of adenosine triphosphate, which provides energy to the cells
[23]. LLLT may be useful in individuals with DM-2, allowing improvements in muscle fatigue and the potentiation of muscle function, with a consequent improvement in exercise capacity and a reduction in the emergence of comorbidities such as diabetic neuropathy.

The hypothesis of the proposed study is that pre-exercise LLLT is capable of improving eccentric muscle performance in individuals with DM-2. If this improvement is confirmed, the use of LLLT can favor the execution of physical exercise and activities of daily living among such patients and avoid the emergence of comorbidities that are common to this disease. LLLT could be widely used in the clinical setting and become an easy-to-administer treatment strategy of considerable value. Moreover, the scientific community is in need of further clinical trials on LLLT involving human subjects for the definition of application parameters, mechanisms of action and the long-term effect on skeletal muscle performance.

The aim of the proposed study is to evaluate the efficacy of pre-exercise LLLT on the performance of the quadriceps femoris (peak torque, total muscle work, maximum power and fatigue index normalized by body mass) in individuals with DM-2.

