## Methods/Design

### Overview of research design

A double-blind, randomized, controlled trial will be carried out. The participants will be allocated to four LLLT groups through a randomization process using opaque envelopes: Group A (4 Joules), Group B (6 Joules), Group C (8 Joules) and Group D (0 Joules; placebo). Evaluations will be performed using multidimensional questionnaire, self-perceived fatigue (visual analog scale for fatigue (VAS-F) and Item 2.2 on the WHOQOL-100), Lower Extremity Functional Scale (LEFS), Diabetes Quality of Life (DQOL) measure, Problem Areas in Diabetes (PAID) scale, WHOQOL-BREF, Patient Specific Functional Scale (PSFS), functional evaluations (isokinetic dynamometer, sit-and-stand test, timed up-and-go test (TUGT), functional reach test (FRT)) and blood collection for the assessment of markers of muscle damage and the capillary glycemia test.

The study will be divided into six evaluations and two treatment phases to which all individuals will be submitted.

#### Evaluation 1

After screening, individuals who meet the eligibility criteria will undergo an initial evaluation involving the multidimensional questionnaire, LEFS, DQOL, PAID, WHOQOL-BREF, PSFS, sit-and-stand test, TUGT and FRT. On a separate day, scheduled based on the availability of the individuals, the blood collection, capillary glycemia test and isokinetic dynamometry (maximum voluntary isometric contraction (MVIC) of the quadriceps muscle) will be performed.

#### Treatment phase 1

Immediately after randomization, treatment will be performed with the administration of the LLLT protocol for the respective groups on the quadriceps muscle bilaterally (alternating legs).

#### Evaluation 2

Immediately following LLLT, the groups will perform the isokinetic eccentric muscle fatigue protocol for the quadriceps muscle bilaterally (alternating legs).

#### Evaluation 3

Immediately after the exercise protocol, blood collection, the capillary glycemia test and isokinetic dynamometry (MVIC of the quadriceps muscle bilaterally (alternating legs)) will be performed.

#### Evaluation 4

Twenty-four hours after the exercise protocol, blood collection, the capillary glycemia test and isokinetic dynamometry (MVIC of the quadriceps muscle bilaterally (alternating legs)) will be performed.

#### Evaluation 5

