**Figure 1 F1:**
[figure not shown]
Realization of isokinetic dynamometry maximum voluntary isometric contraction (MVIC) of the quadriceps muscle.

The volunteers will perform the isokinetic eccentric fatigue protocol for the quadriceps muscle bilaterally (Figure 
2), which will consist of 75 isokinetic eccentric contractions of the knee extensors (5 sets of 15 repetitions with a 30-second rest period between sets) at a velocity of 60°.sec^-1^ in both the eccentric and concentric phases, with a 60° range of motion (between 90° and 30° of knee flexion) for each leg. At each contraction, the dynamometer will automatically (passively) position the knee at 30° and will then flex the knee until reaching 90°. The volunteers will be instructed to resist the knee flexion imposed by the dynamometer with maximum force. The instructions will be given first and the volunteers will receive verbal encouragement throughout the exercise. This protocol has proven to be efficient and reliable for exercise-induced muscle damage
[19].

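### The exclusion criteria allow participants to be excluded after randomisation for muscle injury, and possibly for failing the exercise, events that can be related to treatment and outcome

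*Protocol article*

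**What the plan says.** Two adjacent items in the Exclusion criteria section of the protocol article matter here: "history of skeletal muscle injury in previous six months or during the execution of the study; inability to perform exercise protocol". The second of them reads in full: "inability to perform exercise protocol or undergo evaluations in a satisfactory manner". The section closes with a statement of how they are applied: "Exclusion criteria will be determined by access to medical history of individuals".

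The overview of the research design fixes the order of events. Evaluation 1 comes first and includes the sit-and-stand test, the timed up-and-go test, the functional reach test and an isometric contraction on the dynamometer. Then: "Immediately after randomization, treatment will be performed with the administration of the LLLT protocol". Then: "Immediately following LLLT, the groups will perform the isokinetic eccentric muscle fatigue protocol". Torque and blood markers are measured immediately, 24 hours and 48 hours after the exercise. Phase 2 follows, with 12 sessions over 4 weeks.

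Of the eccentric exercise, the Isokinetic dynamometry section says: "This protocol has proven to be efficient and reliable for exercise-induced muscle damage". The Background gives the hypothesis that "pre-exercise LLLT is capable of improving eccentric muscle performance in individuals with DM-2". The Data analysis section makes peak torque the primary outcome and CK and LDH activity the secondary outcomes, and names a two-way repeated-measures analysis of variance.

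**The concern.** An exclusion criterion protects a randomised comparison only when it is settled before allocation. Here one criterion reaches into the study period, and another may do so. If participants are excluded once they have been treated and exercised, the groups compared are no longer those that randomisation formed, and the reason for leaving may depend on both the treatment and the outcome.

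Two results are at stake. The first is the comparison of the laser groups with placebo on peak torque. The second is the choice of dose: Groups A, B and C all receive in phase 2 whichever protocol gave the best muscle performance in phase 1, so selective exclusion in phase 1 can also affect what is given in phase 2. The word for acceptable performance in the second criterion is not defined, which leaves its use to judgement.

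**Working it through.** **Step 1: when can each criterion be observed?**

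- *Injury in the previous six months*: before enrolment, from the medical history. No problem.
- *Injury during the study*: after enrolment only. A small part of this window lies before randomisation, since Evaluation 1 is spread over separate days. The rest covers the laser treatment, the eccentric exercise, the 48-hour follow-up and phase 2.
- *Inability to undergo evaluations*: partly visible at Evaluation 1, but Evaluations 3 to 6 come after allocation.
- *Inability to perform the exercise protocol*: the exercise is first performed at Evaluation 2, after randomisation and treatment. The article describes no trial run. A judgement at screening is possible but is not described.

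The sentence on medical history fits the first item and perhaps part of the last two. It cannot fit the second, so the section contradicts itself.

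**Step 2: can these events be related to treatment and outcome?** The exercise is 75 maximal eccentric contractions per leg, described as a reliable way to induce muscle damage. The treatment is expected to improve eccentric performance, and the outcomes are torque and two damage markers. An injury or a failure to complete can therefore share causes with the outcome and differ in frequency between groups.

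**Step 3: how large could the bias be?** The article gives no sample size, standard deviation or removal rate, so there is no figure to reproduce. All inputs below are assumptions: outcome normal with SD 1, higher is better, true benefit d = 0.5 SD, and one removal threshold common to both arms.

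If removal is fully determined by the outcome, removing the worst fraction f of an arm raises its mean by φ(z_f)/(1 − f), where z_f is the normal quantile at f.

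- Placebo, f = 0.20: z = −0.842, shift = 0.280/0.80 = 0.350 SD.
- Active, same threshold: z = −0.842 − 0.5 = −1.342, so f is about 0.09, and shift = 0.162/0.910 = 0.178 SD.
- Bias = 0.350 − 0.178 = 0.172 SD. Difference among those kept = 0.5 − 0.172, about 0.33 SD.

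A simulation of 2,000,000 draws, with the correlation between removal criterion and outcome set at 1.0 or 0.5, gave for d = 0.5:

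| Placebo removed | Correlation | Active removed | Difference among those kept |
|---|---|---|---|
| 20% | 1.0 | 8.9% | 0.329 SD |
| 10% | 1.0 | 3.7% | 0.390 SD |
| 10% | 0.5 | 6.3% | 0.469 SD |
| 5% | 0.5 | 2.9% | 0.480 SD |

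The last two rows lose 0.5 − 0.469 = 0.031 and 0.5 − 0.480 = 0.020 SD. Over all scenarios run (d of 0.3, 0.5 or 0.8; 5% to 30% of placebo removed), the retained share of the true difference ran from 54% to 96%.

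**The case against.** The strongest reply is that the criteria are meant for screening. The medical-history sentence points that way, Evaluation 1 would reveal some inability, and an analysis set is normally defined in a full protocol or analysis plan that is not shown. Part of this stands: the inability criterion is ambiguous rather than plainly post-randomisation, and the article nowhere says that data already collected are discarded. It does not rescue the injury criterion, which names the study period itself.

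A reader might infer that everyone excluded has suffered the very damage the laser is meant to prevent. The documents do not support that. If ordinary exercise-induced damage counted as injury, nearly everyone would be excluded, so a clinical injury is the likelier meaning, and it may have nothing to do with the study exercise. The stated hypothesis concerns performance; the damage markers are secondary outcomes. Such events can be consequences of exercise and treatment, but need not be.

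A reader might also pair 20% removal in placebo with 5% in an active group and obtain 0.350 − 0.109 = 0.24 SD. Those rates are freely chosen. With a common threshold and a 0.5 SD benefit, 20% goes with about 9%, and the bias is about 0.17 SD.

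Blinding of participants, therapist, evaluator and statistician limits deliberate removal by group. It does not stop removal rates from differing when treatment changes performance or injury.

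**Conclusion.** The point holds as a defect in the wording. The article permits outcome-related exclusion after randomisation through the injury criterion, possibly also through the inability criterion, and its sentence on medical history conflicts with the former. It does not establish that participants will be deleted from the analysis, or at what rate.

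The size is unknown. Under the assumptions shown, it runs from negligible (0.02–0.03 SD) to about a third of a true 0.5 SD benefit (0.17/0.5 = 34%) at 20% placebo removal with full correlation. In that model the bias is towards no effect. If the laser itself worsened injury or performance, exclusion would instead hide harm.

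**What to change.** 1. Restrict the exclusion criteria to facts established before randomisation, and reconcile the list with the medical-history sentence. If inability to exercise is meant as a screening judgement, say when and how it is assessed.
2. State that a participant with an injury or non-completion after randomisation stays in the analysis in the group as randomised, with all collected measurements.
3. Use a method that keeps incomplete cases, for example a mixed model for repeated measures. Standard repeated-measures analysis of variance drops anyone with a missing time point, so the statement in item 2 would have no effect without this. As missing torque may depend on the unobserved value, add a sensitivity analysis.
4. Report injuries and non-completions by group as results.

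The cost is a few sentences, somewhat more analysis work and possibly more variable estimates. Recruitment is already under way, so anyone already excluded after randomisation under these criteria should be identified and accounted for by group. The clinical handling of an injured participant is left to the investigators.

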### Ethical considerations

The proposed study received approval from the local Human Research Ethics Committee under process number n° 164549 dated 5 December 2012. The study will be conducted in compliance with the norms that regulate research involving human subjects contained in Resolution n° 196/97 of the Brazilian National Health Council. The study is registered with the World Health Organization under Universal Trial Number U1111-1146-7109.

All participants will be informed regarding the objectives and procedures of the study and will be asked to sign a statement of informed consent agreeing to participate.

### Procedures

#### Questionnaires

At the beginning (Evaluation 1) and end (Evaluation 6) of the study, the following questionnaires will be employed:

– A multidimensional questionnaire drafted by the researchers addressing clinical and socio-demographic variables (gender, weight, height, age, marital status, time elapsed since the diagnosis of DM-2, schooling, other diagnosed conditions, medications in use and dose of medications in use).

– LEFS: developed in English to evaluate musculoskeletal disorders of the lower limbs
[24], the LEFS consists of 20 items addressing different activities. Each item has a five-option response scale, which is scored as follows: 0 (extreme difficulty or unable to perform); 1 (quite a bit of difficulty); 2 (moderate difficulty); 3 (a little bit of difficulty); and 4 (no difficulty). The maximum score is 80 points, with lower scores denoting greater difficulty
[25]. The LEFS has been adapted and validated for Portuguese, with Cronbach’s alpha = 0.95
[25].

– DQOL: this questionnaire has 46 multiple-choice items for the evaluation of quality of life among individuals with diabetes and is made up of four subscales: satisfaction, impact, social/occupational worries and worries related specifically to diabetes. The response options are organized on a five-point Likert scale: 1 = very satisfied; 2 = quite satisfied; 3 = moderately satisfied; 4 = somewhat dissatisfied; and 5 = completely dissatisfied. For the impact and worries subscales, the items are scored as follows: 1 = never; 2 = rarely; 3 = sometimes; 4 = often; and 5 = always. Lower scores denote a better quality of life
[26]. The DQOL has been translated and validated for Portuguese and demonstrates adequate reliability and validity for patients with DM-2
[26].

– PAID: questionnaire composed of 20 items on the emotional state of individuals with DM (types 1 and 2). Each item has a five-point Likert response scale: 0 = not a problem; 1 = small problem; 2 = moderate problem; 3 = nearly a serious problem; and 4 = serious problem. The score ranges from 0 to 100 points, with higher scores denoting a greater degree of emotional suffering
[27]. The Portuguese version will be used in the proposed study, which has a Cronbach’s alpha = 0.93 for patients with DM-2
[28].

– WHOQOL-BREF: this questionnaire is the short form of the WHOQOL-100, which was developed by the Quality of Life workgroup of the World Health Organization and has previously been used on individuals with DM-2
[29]. The questionnaire is made up of 26 items, two on global and general health and the others distributed among four subscales: physical health, psychological health, social relations and environment. Each item is scored using a Likert scale (1 to 5 points). The results are transformed into a linear scale (0 to 100), with higher scores denoting a better quality of life
[30]. The Brazilian version of the WHOQOL-BREF has demonstrated satisfactory internal consistency for both the items and subscales and is a useful tool for the evaluation of quality of life in the Brazilian population
[31]. This questionnaire will be administered during Evaluations 1 and 6 and will also be administered by telephone 3 and 6 months after Evaluation 6.

– PSFS: the aim of this self-report scale is to evaluate functional changes, especially those related to the musculoskeletal system. This scale can be used for any part of the body in individuals with different degrees of functionality and different diseases. Function is self-rated on five activities the individual considers important and is having difficulty performing or is unable to perform. Each activity identified by the individual is rated using an 11-point Likert scale (0–11 points), for which higher scores denote greater functionality
[32].

– Self-perceived fatigue: subjective fatigue following the MVIC and isokinetic eccentric exercise protocol of the quadriceps muscle will be determined using the VAS-F and item F2.2 on the WHOQOL-100 (physical subscale). For the VAS-F, a color scale measuring 50 cm in length will be printed on a piece of paper, beginning with light blue (minimum) and proceeding to intense red (maximum). The individual will mark their subjective evaluation of muscle fatigue on the scale. On the other side of the card, the examiner will have access to a numeric scale ranging from 0 (minimum) to 10 (maximum) and record the value corresponding to the subject’s mark on the opposite side. Only the examiner will have access to the numeric scale
[33,34].

All questionnaires will be administered in a reserved room and are to be filled out completely. If an individual refuses or is unable to cooperate, Examiner 2 will mark “NR” (no record) in capital letters on the exam. To avoid hurried responses from the participants, no time constraints will be applied.

#### Functional assessment tests

– Sit-and-stand test: a standardized chair will be used for all individuals, with an adjustable height to maintain the knees flexed at 90° and no arm rests. Sit-and-stand was chosen due the fact that this movement is one of the activities of daily living of greater demand in terms of mechanical aspects
[35]. The individual will be instructed to sit down and stand up from the chair five times. The execution time will be recorded with the aid of a stopwatch (OREGON^©^ - Oregon Scientific Brasil LTDA – http://www.oregonscientific.com - [name]. [contact]).

– TUGT: this test has been used to evaluate function in individuals with DM-2
[36]. The TUGT measures functional mobility based on the time required to stand up from a chair, walk three meters, turn around, walk back to the chair and sit down again. The test will begin with the verbal command “go” and will end when the participant is once again seated in the chair. The execution time will be recorded with the aid of a stopwatch (OREGON^©^). The test will be performed once for the participant to become familiarized with the procedure and the second trial will be used to record the execution time. A standardized chair will be used for all individuals, with an adjustable height to maintain the knees flexed at 90° and no arm rests
[37]. The following are the reference parameters for this test: 10 seconds for healthy, independent adults with no risk of falls; 11 to 20 seconds for elderly individuals with disability or frailty; and greater than 20 seconds for elderly individuals with important mobility impairment and a risk of falls
[38].

– FRT: this test measures the maximum distance an individual can reach forward beyond the length of his/her arm while maintaining a fixed standing base. The FRT has been used to determine movement strategies in patients with DM
[39]. A reach less than 15 cm indicates frailty and an eminent risk of falls
[40]. A metric tape will be attached to the wall parallel to the ground at the height of the individual’s acromion. The participant will be barefoot with the feet aligned and standing next to the beginning of the tape measure, with the wrists in a neutral position, elbows extended and the shoulder flexed at 90°. The individual will be instructed to lean forward without touching the tape. The movement of the wrist over the tape will be read three times and the mean will be used for the analysis
[39].

#### Blood collection

Blood samples (10 ml) will be collected through the antecubital vein by an experienced nurse. One hour after collection, the samples will be centrifuged at 3,000 rpm for 20 minutes. Pipettes will be used to transport the serum to Eppendorf® tubes (Eppendorf, Hamburg, Germany) which will be stored at -80°Cuntil analysis. Enzyme activity of creatine kinase (CK; CK-MB, CK-MM and CK-BB) and lactate dehydrogenase (LDH; LHD1,2,3,4,5) will be analyzed. The biochemical markers of muscle damage will be analyzed in a clinical laboratory
[41,42].

Capillary glycemia will be monitored by the individuals themselves. The use of the equipment will be explained prior to the procedure. Blood will be taken from the palm side of the tip of the third finger on the right hand using a digital blood sugar meter (Accu-Chek® Performa nano; Roche Diagnosis ([name]) and lancet (Accu-Chek® multiclix; Roche Diagnostics ([name])). The lancet will be standardized at the deepest penetration (number 5). The measure of capillary glycemia and fast, highly precise digital monitors is currently considered the gold standard for at-home blood sugar control in patients with DM and will be used in the present study to determine the oscillation in blood sugar in the different phases of the study
[43].

